## Abstract

In addition to general anesthesia and mechanical ventilation, robotic-assisted laparoscopic radical prostatectomy (RALP) necessitates maintaining a capnoperitoneum and placing the patient in a pronounced downward tilt (Trendelenburg position). While the effects of the resulting fluid shift on the cardiovascular system seem to be modest and well tolerated, the effects on the brain and the blood–brain barrier have not been thoroughly investigated. Previous studies indicated that select patients showed an increase in the optic nerve sheath diameter (ONSD), detected by ultrasound during RALP, which suggests an elevation in intracranial pressure. We hypothesize that the intraoperative fluid shift results in endothelial dysfunction and reduced cerebral clearance, potentially leading to transient neuronal damage. This prospective, monocentric, non-randomized, controlled clinical trial will compare RALP to conventional open radical prostatectomy (control group) in a total of 50 subjects. The primary endpoint will be the perioperative concentration of neurofilament light chain (NfL) in blood using single-molecule array (SiMoA) as a measure for neuronal damage. As secondary endpoints, various other markers for endothelial function, inflammation, and neuronal damage as well as the ONSD will be assessed. Perioperative stress will be evaluated by questionnaires and stress hormone levels in saliva samples. Furthermore, the subjects will participate in functional tests to evaluate neurocognitive function. Each subject will be followed up until discharge. Conclusion: This trial aims to expand current knowledge as well as to develop strategies for improved monitoring and higher safety of patients undergoing RALP. The trial was registered with the German Clinical Trials Register DRKS00031041 on 11 January 2023.

## 1. Introduction

A sudden change in body position leads to rapid fluid shifts that are well compensated by the cardiovascular system in combination with an acute catecholaminergic stress response. Prolonged fluid shifts, however, may not be completely compensated for (e.g., standing for several hours and subsequent peripheral edema). In addition to general anesthesia and mechanical ventilation, robotic-assisted laparoscopic radical prostatectomy (RALP) requires maintaining a capnoperitoneum and placing the patient in a steep downward tilt (Trendelenburg position). The effects of the resulting fluid shift on the cardiovascular system seem to be modest and well tolerated [1,2]. The intracerebral physiology under these conditions and how these conditions affect intracranial pressure (ICP) and cerebral perfusion pressure (CPP) is less clear.

In animal models, it has been shown that the invasively measured ICP can increase by up to 10 mmHg due to the capnoperitoneum and the downward tilt [3,4,5,6,7,8]. In humans, a non-invasive estimation of the intracranial pressure and the detection of increased intracranial pressure can be achieved with the help of ultrasound-guided measurement of the optic nerve sheath diameter (ONSD). A non-invasive method to estimate changes in the ICP in humans is to measure the optical nerve sheath diameter (ONSD) using ultrasound [9,10,11]. Several studies on patients undergoing RALP have shown that the ONSD can increase significantly [12,13,14]. A study from 2014 observed a 12.5% increase in the ONSD in a small subset of these patients (three out of twenty). ONSD values corresponding to an ICP of over 20 mmHg were observed in patients who showed valve insufficiency of the internal jugular vein (IJV) during RALP [14]. In addition, the choice of the anesthesia protocol seemed to affect the compensatory mechanisms. The intracranial autoregulation of the human body can maintain an adequate CCP in most situations. Only when these mechanisms are exhausted do severe complications occur [15,16]. In this context, it has been shown that using total intravenous anesthesia with propofol instead of employing an anesthetic gas (e.g., desflurane or sevoflurane) seemed to be beneficial [17,18].

The effect on postoperative cognitive performance in this patient population remains underinvestigated and is therefore not conclusively understood. Patients with a high intraoperative ONSD are more likely to appear disoriented during the awakening period or in the recovery room [19]. Due to the increasing use of RALP (80% of radical prostatectomies in the USA [20]), it is important to better investigate neurological complications and to develop a better monitoring strategy and awareness of potential transient brain damage. Some studies did not detect a cognitive deficit in patients after RALP [13]. Others, however, showed a lower outcome in standardized tests such as the mini-mental state examination (MMSE) in patients who experienced intraoperative IJV valve insufficiency [14]. Additionally, an increased risk of postoperative delirium was noted [21].

The correlation between postoperative (emergence) delirium and the observed intraoperative valve insufficiency suggests that an intraoperative fluid shift might occur leading to an endothelial dysfunction and reduced cerebral clearance, possibly resulting in transient neuronal damage. A very specific biomarker for neuronal damage that is increasingly gaining importance is the axonal protein neurofilament light chain (NfL) [22]. Previous work showed that NfL might serve as a prognostic marker not only in neuronal disease states but also in several other patient groups, e.g., after cardiac arrest [23,24] and cardiac surgery [25,26].

Research on astronauts, previously conducted by our team, showed that long-term space missions and exposure to microgravity may induce a cephalad fluid shift resulting in an elevation of biomarkers for traumatic brain injury and neurodegeneration in blood [27]. Using the highly sensitive single-molecule array (SiMoA) before and after a long-term space mission (mean duration 169 days), a significant increase in NfL and glial fibrillary acidic protein (GFAP, a biomarker for neurotrauma) was detected. This was likely due to the long-lasting pressure caused by the fluid shift in microgravity and the restitution of the blood–brain barrier after return to Earth. These changes correlated with volumetric brain tissue changes observed in magnetic resonance images (MRI) in the very same group [28,29]. A long-term space mission is significantly different from RALP and cannot be compared. However, the data showed that even in healthy individuals blood-based biomarkers for brain damage may serve as a monitoring tool for transient brain damage due to cephalad fluid shifts.

We hypothesize that the pronounced downward tilt in RALP in combination with the capnoperitoneum and general anesthesia may restrict physiological adaptation mechanisms resulting in reduced endothelial integrity and a fluid shift into the tissue. These processes might lead to a detectable increase of blood biomarkers for brain damage and changes in the ONSD. The prospective UroTreND Study aims to create a better understanding of cerebral and hormonal autoregulation and pathomechanisms in patients undergoing RALP compared to patients who are scheduled for the conventional open technique. Furthermore, the study shall support the development of strategies for improved monitoring tools such as the ONSD and thus further the safety of patients undergoing RALP.

## 2. Outcome Measures

### 2.1. Primary Endpoint

The primary endpoint of this study is the perioperative concentration of NfL in plasma (single-molecule array (SiMoA)).

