### 3.2. Timeline for Each Patient

After informed consent to participate in the study has been given, the baseline time point T0 will take place. On the day of the surgery, there are three time points scheduled: T1 after the induction of anesthesia, T2 1–2 h after incision, and T3 during emergence, after the patient has been repositioned. The follow-up period will consist of T4 on postoperative day one, T5 on postoperative day three, and T6 before discharge (usually postoperative days 5–7). An overview of the patients’ schedule of activities according to the standard protocol items—recommendations for interventional trials (SPIRIT)—is provided in Figure 1.

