### 3.5. Sample Size Estimation

The experimental group (n = 30) will receive RALP while the control group (n = 20) will receive a conventional open radical prostatectomy. Thus, a total of 50 patients will be included. Each patient will choose the preferred method for himself. To obtain homogenous groups, attention will be paid to a balance of the preoperative risk assessment (ASA score) in both groups.

We hypothesize that the postoperative NfL concentration will be higher in the experimental group compared to the control group. To date, NfL has not been evaluated in this patient population. However, it is expected that the increase in the NfL concentration will be minor in the control group compared to the experimental group. Although the temporal dynamics are currently unknown, we expect an increase between the preoperative measurement point and the postoperative measurement points until discharge (usually days 5–7).

In a recent study comparing patients after bypass surgery with patients after neck surgery, an increase in concentration of NfL was found on the seventh postoperative day using SiMoA. The sample size of this study group was 25 and the control group was 26 [30]. In patients undergoing neck surgery, no NfL was detected. This trial will also employ SiMoA. RALP may be different from bypass surgery; however, a risk of neuronal damage can be assumed, and previous work showed an increased ICP in a similar group strength [12,13]. We therefore estimated the required sample size in the experimental group to be 30 patients. It may, however, be possible that NfL is detectable in the control group and increases over time but to a lesser extent or in a narrower time window. Thus, we expect a smaller dispersion of detectable changes in the control group. Everything considered, we calculated the control group to be up to 20 patients.

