### 3.6. Statistical Evaluation

The exact case number can only be approximated due to the lack of previous studies in this patient population. The obtained data from each patient will be analyzed individually. After testing for normal distribution (Kolmogorov–Smirnov test), the appropriate statistical test for comparison will be selected (e.g., repeated measurements ANOVA or Friedman test). The median, mean values, and standard deviations will then be calculated from the generated data sets of all patients. The data will be statistically analyzed using the software SPSS 24.0 (IBM, New York, NY, USA) and Sigma Plot 13 (Chicago, IL, USA). A significance level α of 0.05 and a statistical power of 0.8 were defined for this study. A flow chart of the trial is provided in Figure 2.

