## 4. Analysis Methods

Blood samples will be taken at all time points T0–T6. The ONSD will be measured at T0–T4. Functional tests and questionnaires will be conducted at T0/T1 and T3–6 simultaneously for saliva collection. Urine samples will be taken, when possible, at T1 and T3/T4. The MRI scan will be performed at T0 and T4. An overview of the samples and procedures employed at each time point is provided in Figure 3.

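### The primary endpoint, perioperative NfL, fixes no time point or group contrast, and no test the protocol names is a single test of its postoperative between-group hypothesis

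*Protocol article*

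**What the plan says.** The primary endpoint (section 2.1) reads "The primary endpoint of this study is the perioperative concentration of NfL in plasma (single-molecule array (SiMoA". The abstract uses the same adjective and also names no time point.

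Section 4 says "Blood samples will be taken at all time points T0–T6". Section 3.2 places the samples. T0 is the baseline after consent. The day of surgery has "T1 after the induction of anesthesia, T2 1–2 h after incision, and T3 during emergence, after the patient has been repositioned". Follow-up has "T4 on postoperative day one, T5 on postoperative day three, and T6 before discharge (usually postoperative days 5–7".

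The hypothesis (section 3.5) is narrower than the endpoint, and directional: "We hypothesize that the postoperative NfL concentration will be higher in the experimental group compared to the control group". The same section adds: "Although the temporal dynamics are currently unknown, we expect an increase between the preoperative measurement point and the postoperative measurement points until discharge".

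Section 3.6 offers repeated-measures ANOVA or the Friedman test as examples, to be selected after a normality test. It names no between-group contrast. It also states "A significance level α of 0.05 and a statistical power of 0.8 were defined for this study". The group sizes are in section 3.5: "The experimental group (n = 30) will receive RALP while the control group (n = 20) will receive a conventional open radical prostatectomy".

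**The concern.** Endpoint and hypothesis do not describe the same quantity. Of the seven samples, T0 and T1 are taken before incision and T2 during surgery. That T1 also precedes the head-down tilt is inferred from the order in section 3.2, not stated there. At most four samples (T3–T6) bear on a postoperative hypothesis, and only T4–T6 lie in the stated follow-up period.

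The named tests do not close the gap:

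- **Repeated-measures ANOVA, group effect.** It compares the arms on the average of all samples, including those in which the hypothesis predicts no difference.
- **Repeated-measures ANOVA, group-by-time term.** It asks whether the two time profiles differ in shape. It has no direction, and it responds to a purely intraoperative difference.
- **Friedman test.** It is a within-patient test over time and cannot compare robotic with open surgery. If it is selected, the group comparison passes to a test that is not named.

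The protocol says the time course is unknown, so the choice of time point or contrast is open to being made after the data are seen. At stake is whether the trial's one primary result is a test of its stated hypothesis at the stated error rate.

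**Working it through.** **Inputs from the protocol.** 30 robotic and 20 open patients; alpha 0.05; power 0.80; seven samples.

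**Assumptions, because the protocol gives no values.** Two-sided tests, equal SD at every sample, a common correlation ρ of 0.5, 0.7 or 0.85 between samples, no dropout, and the same standardised difference δ at every affected sample.

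**1. The plan's own figure.** N = 50 cannot be reproduced, because no effect size, SD or time point is given. Solving backwards for a single sample: δ = (1.960 + 0.842) × √(1/20 + 1/30) = 2.802 × 0.2887 = 0.81 SD by the normal formula, or 0.825 (about 0.83) with the t distribution. One postoperative sample therefore has 80% power by construction, which confirms nothing about the plan.

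**2. Group effect over all seven samples.** If m of the seven samples differ by δ, the mean difference is (m/7)δ and the variance of a patient's mean is (1 + 6ρ)/7. The noncentrality is (m/7)δ / √[((1 + 6ρ)/7)(1/20 + 1/30)] on 48 df.

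Example, T4–T6 only and ρ = 0.7: (3/7) × 0.825 = 0.354; 0.354 / (0.862 × 0.2887) = 1.42; power 29%.

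| Arms differ at | Share of δ kept | ρ = 0.5 | ρ = 0.7 | ρ = 0.85 |
|---|---|---|---|---|
| T4–T6 | 3/7 | 36% | 29% | 25% |
| T3–T6 | 4/7 | 56% | 46% | 40% |
| T2–T6 | 5/7 | 75% | 64% | 57% |

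**3. Separate tests of T3–T6, each at 0.05.** Independent tests would give 1 − 0.95⁴ = 18.5% false positives. Simulating four correlated z statistics (400,000 draws) gives 15.6%, 13.1% and 10.5% at ρ = 0.5, 0.7 and 0.85.

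**4. Group-by-time term.** λ = [30 × 20/50] × m(1 − m/7)δ² / (1 − ρ), on 6 and 288 df, sphericity assumed.

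- T4–T6 differ, ρ = 0.5: λ = 12 × 3 × (4/7) × 0.681 / 0.5 = 28.0; power 99%. It is higher at larger ρ. For T2–T6 it is 97% or more.
- Only T2 differs, ρ = 0.5: λ = 12 × (6/7) × 0.681 / 0.5 = 14.0; power 80%, rising to nearly 100% at ρ = 0.85.
- λ depends on δ², so the power is the same if the open arm is the higher one.

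The test is undiluted and is one test at 0.05. A significant result does not establish a higher postoperative level after robotic surgery.

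**5. One T0-adjusted postoperative mean over k samples.** The residual variance is (1 + (k − 1)ρ)/k − ρ². Power at ρ = 0.5 / 0.7 / 0.85:

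| Arms differ at | Adjusted mean T4–T6 | Adjusted mean T3–T6 |
|---|---|---|
| T4–T6 | 99% or more throughout | 93 / 98 / over 99% |
| T3–T6 | 99% or more throughout | 99% or more throughout |
| T3–T4 only | 30 / 39 / 60% | 63 / 75 / 93% |

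Without T0 adjustment, the T4–T6 mean has 93 / 88 / 84% power when T4–T6 differ. The gain over step 2 therefore comes partly from dropping the early samples and partly from using the baseline.

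**The case against.** A reader might infer that the effect will be diluted or else the error rate will be inflated. The documents do not support that. Section 3.6 lists its tests as examples. It says neither that the seven samples will be averaged nor that each will be tested. The group-by-time term of the ANOVA it names avoids both problems (step 4). What remains is that this term does not answer a directional postoperative question, and the follow-up contrasts needed to read it bring multiplicity back.

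A reader might also quote the false-positive rate for seven separate tests, about 13–23%. That overstates the risk, because a difference at T0 or T1 could not be read as support for a postoperative hypothesis. T3–T6 is the fairer count. Quoting only the T4–T6 dilution pattern would be one-sided too, since T3 follows repositioning.

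It can be said that perioperative includes postoperative, and that the preoperative sample is the reference for the expected rise. Both are true, so this is an imprecise endpoint that fails to match the hypothesis rather than an outright contradiction. Section 5.1 also calls the study a pilot aiming at first insights, but section 3.6 still sets an alpha and a power.

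Finally, an analysis plan not shown may fix the contrast and any multiplicity rule, and their absence here is not the point. The article itself states the primary endpoint, the hypothesis and the candidate tests, and these do not fit together.

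**Conclusion.** The point holds in this form: the primary endpoint fixes no time point or between-group contrast, does not match the postoperative hypothesis, and is paired with tests none of which is a single test of it. The mismatch itself rests on the text and needs no assumption.

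The consequences are conditional on the analysis chosen later. If the seven-sample group effect is used, power may fall from 80% to somewhere between about 25% and 75%, depending on which samples differ. If T3–T6 are tested separately, the error rate may rise to about 10–16%. These figures rest on the back-solved 0.83 SD, a common correlation of 0.5–0.85 and equal SDs, none of which is in the protocol. They do not show that the trial as planned is underpowered or that its error rate is inflated.

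**What to change.** Before recruitment, redefine the primary endpoint as one prespecified between-group contrast of postoperative log NfL adjusted for T0. An example is the robotic-minus-open difference in the mean over the postoperative samples, tested once at 0.05 with sidedness stated. The sponsor should fix in advance whether T3 belongs to the window, and make the other samples and single time points secondary or descriptive. The sample-size section should refer to this endpoint.

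The cost is a change of wording in the protocol, and in the registry entry if it uses the same wording. No patients, samples or assays are added, and the sampling days need not change. Section 5.2 describes the trial as still in preparation, so on the document's own account the change precedes the data.

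The downside is that a difference outside the chosen window is missed, and one confined to part of it is diluted. If only T3 and T4 differ, a T4–T6 mean has about 30–60% power and a T3–T6 mean about 63–93%. Because the time course is unknown, the window is a judgement for the sponsor; several choices would close the gap.

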### 2.2. Secondary Endpoints

Secondary endpoints are as follows:The markers of endothelial and blood-brain barrier function in the blood (matrix metalloproteinases-2 and -9, zonulin, S100 calcium-binding protein B (S100B), neuron-specific enolase (NSE), GFAP, amyloid-β proteins 40 and 42 (Aβ40, Aβ42), and glycocalyx proteins (e.g., hyaluronan, syndecan-1, and heparan sulfate));The estimation of ICP through measuring the ONSD using ultrasound and a short screening of extracranial cervical blood vessels for valve insufficiencies;Neurocognitive function (MMSE, clock drawing test, Nu-DESC, memory test);The physiological parameters of stress (cortisol in saliva and urine, current stress test (CST));The presence and severity of headache;Immune analyses (differential, leukocyte subsets, plasma cytokines, cell adhesion molecules, markers of cellular activation, radical production, phagocytosis);The analysis of immune cell signaling cascades using transcriptional analysis (mRNA) and Western blot (whole blood, PBMCs, isolated neutrophils);Procedure-related parameters (end-tidal CO_2_, type of anesthesia protocol, use of anesthetic gas, blood loss, mean arterial pressure, incision–suture time, total time of anesthesia);An MRI scan of the cerebrum (optional).

The detection method for each endpoint is listed under “4. Analysis methods”.

## 3. Trial Design

The UroTreND Study is a single-center, interventional, non-randomized, prospective clinical trial. It will be conducted at the LMU University Hospital Munich, Germany. The trial was registered under the German Clinical Trial Register (Trial number: DRKS00031041).

### 3.1. Recruitment

Potential subjects will be identified at the outpatient clinic of the urology or anesthesiology department based on their diagnosis or scheduled surgery. Due to the investigated procedure, only male subjects will be eligible for recruitment. Only patients presenting with organ-centered tumors who are scheduled for a radical prostatectomy either in the robotic-assisted or in the conventional open technique will be recruited. In most cases, patients will choose their preferred method of surgery. No science team member will influence the choice of the type of procedure and no randomization will be performed. Each patient will receive all standard preoperative examinations (e.g., cardiac and pulmonary auscultation). We will screen eligible patients for study participation according to the selection criteria. Information regarding the trial and study-specific procedures will be provided during an interview with a member of the study team. Informed consent will be obtained from all subjects. In addition to the informed consent to trial participation, the patient will be asked to provide a separate signature for the MRI scan. The latter consent is independent of participation in the study. The subject will be informed that the MRI scan is optional. We will inform all subjects who receive an MRI about scheduling, risks, and benefits, especially the risk of incidental findings in the brain. Patients will receive an adequate amount of time to think about their choice (in most cases, weeks) before they sign a written informed consent to participate in this study.

### 3.2. Timeline for Each Patient

After informed consent to participate in the study has been given, the baseline time point T0 will take place. On the day of the surgery, there are three time points scheduled: T1 after the induction of anesthesia, T2 1–2 h after incision, and T3 during emergence, after the patient has been repositioned. The follow-up period will consist of T4 on postoperative day one, T5 on postoperative day three, and T6 before discharge (usually postoperative days 5–7). An overview of the patients’ schedule of activities according to the standard protocol items—recommendations for interventional trials (SPIRIT)—is provided in Figure 1.

